#### Analysis of outcome variables

There will be one analysis of depression and health related quality of life after completion of the trial, i.e. no interim analyses are planned for the primary parameters. The primary response variable is the z-transformed SF-36 Mental Component Summary (MCS) score at the one-year follow-up. We plan to employ a linear regression model of z-transformed SF-36 score on type of intervention and baseline score. Additional variables (e.g. gender, age, centre, and illness severity) may be included in the model, if indicated.

The hypotheses will be ordered hierarchically (1: CBT vs. TAU, 2: CBT vs. SH); the second hypothesis will be tested at a two-sided 5% level only if the first test is significant at a two-sided 5% level. Analyses will be performed using an intent-to-treat analysis, and the last observation carried forward method will be used for the handling of missing data. Secondary outcomes (HRQoL (physical component), severity of depression, prophylaxis of moderate/severe major depression, glycaemic control (HbA1c), and mortality) will be analysed primarily in a descriptive manner. For binary response variables, the numbers and proportion of responders will be presented together with 95% confidence intervals for the proportions; continuous variables will be analysed by use of summary statistics. If differences between intervention groups are investigated, outcomes will be adjusted for baseline values through use of appropriate models (linear, logistic, or Poisson regression); however, the p-values for such secondary analyses may not be interpreted as confirmatory findings. Subgroup analyses stratified for gender (male/female), mild cognitive impairment (yes/no), and number of previous depressive episodes (<3, ≥3) also will be carried out. These analyses will be conducted using the same methods as those for the full population. Time to onset of moderate/severe major depression and conversion rates to dementia will be analysed using Kaplan-Maier estimates.

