### Trial interventions

Patients included in the MIND-DIA trial will be randomized to one of the three treatment arms. Within group interventions, all sessions will be videotaped and supervised by psychotherapists. Adherence to treatment will be evaluated by a rating system.

(1) CBT is a manualised diabetes-specific cognitive behavioural therapy, delivered by trained psychologists in small groups (4 to 8 participants) in an outpatient setting. CBT is based on a manualised programme (12 weekly sessions) designed for older adults with type 2 diabetes; the treatment includes cognitive and behavioural strategies to overcome depression and diminish diabetes-related distress, reduce perceived barriers to various aspects of self-management, increase physical activity, and enhance coping skills. Central elements are psychoeducation, support, problem solving, pleasant activities, scheduling of physical activity by use of pedometers, thought-control techniques, cognitive restructuring, Socratic dialogue, training in social skills and interpersonal contact, crisis intervention, and emergency planning. In terms of a workbook, theoretical background, worksheets, and exercises are given to the patients. An important element of the CBT condition is the adoption of pedometers to increase patients' activity levels. For seven days prior to the start of the intervention, patients will wear a sealed pedometer to determine their baseline activity. During the first week of the trial, patients will not change their usual activity level. At the start of the intervention, there will be one session in which information will be provided to the patients about the link between the amount of walking and improvements in health and about general consequences of doing more walking. Patients will be asked to set themselves specific weekly (or monthly) goals regarding the number of steps they will take based on their individual baseline measurements. In addition to the daily step measurements, the number of steps will be recorded by the pedometer on a weekly basis. Furthermore, patients will receive weekly feedback on their physical activity level in the form of graphic and written information. After 12 weeks of open-label therapy, the CBT intervention will be reduced to one session per month during the long-term phase of the trial. The topics of the short-term sessions will be replicated during the long-term phase in order to increase the therapeutic power of the intervention.

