(2) The manualised, guided self-help intervention 'Successful ageing with Diabetes' (SH), with a focus on living and ageing with diabetes, will be delivered by trained moderators (elder-care nurses, nurses, educators, or others). Moderators should pay attention, be empathetic, and give support to all patients. The guided self-help intervention will provide an intact community and a sense of belonging. This procedure will enable the investigators to control for unspecific group effects due to participation in a social network of people who share the same problems; such participation may reduce social or emotional isolation. The moderators should promote reciprocal caring and the sharing of relevant information regarding diabetes and ageing. The primary value of this group condition will be the mutual aid offered by members to one another. Therefore, no formal therapeutic aspects will be involved; moderators should restrict their function to guiding the group and giving support. The intervention is based on a manualised programme, which comprises only recommendations for group sessions. Patients primarily choose the topics or group activities. Thematically, the intervention modules will be comparable to the programmes of German self-help groups; such programmes consist of spontaneous conversation or several group activities.

(3) The participants in the TAU group and their treating physicians will receive diagnostic feedback regarding minor or mild depressive symptoms and cognitive function. Furthermore, feedback on the therapeutic options will be given to the physicians if minor or mild depressive symptoms are diagnosed. For minor depression or depressive symptoms on a subclinical level, the following treatment options, including combinations of them, are generally possible:

• 'watchful waiting' (to await the spontaneous remission of the disorder)

• psychotherapy and/or physical activity

• currently, there is no scientific evidence for medical treatment with antidepressants in elderly diabetes patients with minor depression, but a treatment attempt with a well-tolerated antidepressant (e.g. sertraline or citalopram) could be an optional medical intervention.

However, any treatment option may be chosen, since care as usual for sub-threshold depression is currently not formalised.

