### Statistical analysis

#### Sample size calculation

The power calculation is based on expected differences in SF-36 z-scores. Based on our own comparison of type 2 diabetes patients with mainly untreated depression versus non-depressed patients, we assume differences of δ = 0.6 between CBT and TAU and of δ = 0.4 between CBT and SH. For the latter comparison, a significant difference can be detected with a power of 90% if n = 132 patients per intervention group are enrolled (2-sided t-test, α = 0.05). Given 132 patients in the CBT group, it is sufficient to enroll 51 patients in the TAU group to achieve a power of 95% for the comparison CBT vs. TAU. We therefore plan to recruit a total number of 315 patients (132 in CBT, 132 in SH, and 51 in TAU). We expect a rate of loss to follow-up of 20% in light of our experiences in the ongoing Depression and Diabetes (DAD) study and assuming that mortality will play a role in our sample because of the age of the patients. Analyses will be performed using an intent-to-treat principle (ITT) that includes all randomised subjects in the groups to which they were assigned. The last observation carried forward method (LOCF) will be used for the handling of missing data due to dropouts. The primary population for analysis is the ITT population. To fully appreciate the potential influences of missing responses and the LOCF method chosen as imputation procedure, additional sensitivity analyses examining the effects of different imputation methods will be performed and discussed.

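### CBT and SH are group treatments, but the stated primary model and sample size treat all patients as independent, so the 5% level is at risk, mainly for CBT vs SH

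*Protocol article*

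**What the plan says.** All references are to the protocol article.

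- **CBT delivery** (Trial interventions): "delivered by trained psychologists in small groups (4 to 8 participants) in an outpatient setting".
- **SH delivery** (Trial design; Trial interventions): SH is the second of the two group interventions, which both drop to monthly sessions after 12 weeks. A moderator guides it, and its benefit is meant to come from the other members: "The primary value of this group condition will be the mutual aid offered by members to one another". No SH group size is given.
- **TAU** (Trial interventions): the patient and the treating physician receive diagnostic feedback, and any treatment option may be chosen. There is no group.
- **Primary model** (Analysis of outcome variables): "We plan to employ a linear regression model of z-transformed SF-36 score on type of intervention and baseline score". Gender, age, centre and illness severity are named as possible further covariates. Therapy group is not named.
- **Order of tests** (same section): CBT vs TAU first, then CBT vs SH, each at a two-sided 5% level.
- **Sample size** (Sample size calculation): "we assume differences of δ = 0.6 between CBT and TAU and of δ = 0.4 between CBT and SH", and for CBT vs SH "a significant difference can be detected with a power of 90% if n = 132 patients per intervention group are enrolled", by two-sided t-test. TAU is then set at 51 for 95% power. No ICC or design effect appears.

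**The concern.** Patients who attend the same sessions influence one another and have whoever leads the group in common, so their outcomes may be alike. For SH the article names this mutual influence as the way the treatment works, which sits badly with an assumption of zero within-group correlation. The design is partially nested: two arms clustered by therapy group, one arm not.

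Ordinary regression counts each patient as a separate piece of information. With a positive ICC it understates the standard error, so p-values are too small and confidence intervals too narrow. The more exposed test is CBT vs SH, where both arms are clustered. That comparison is the second confirmatory test, it sets n = 132, and it carries the claim that CBT has a specific advantage beyond meeting in a group.

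**Working it through.** **Inputs from the article.** α = 0.05 two-sided; δ = 0.4 (CBT vs SH) and 0.6 (CBT vs TAU); n = 132, 132 and 51; CBT group size m = 4 to 8.

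**Assumptions, not in the article.** SD = 1, implied by the z-score scale; ICC 0.01 to 0.10; SH groups the same size as CBT groups, except where stated.

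**Step 1: the plan's own figures.** Normal approximation:

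- n per arm = 2 × (1.96 + 1.2816)² / 0.4² = 131.3, rounded up to 132.
- CBT vs SH: SE = √(2/132) = 0.1231; power = Φ(0.4/0.1231 − 1.96) = 90.1%.
- CBT vs TAU: SE = √(1/132 + 1/51) = 0.1649; power = Φ(0.6/0.1649 − 1.96) = 95.3%.

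The noncentral t gives 89.9% and 95.2%. The stated 90% and 95% are thus fully explained by independent patients, with no allowance for clustering.

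**Step 2: add clustering.** The design effect is DE = 1 + (m − 1) × ICC.

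- CBT vs SH: true SE = √(2·DE/132), so the ratio of true to naive SE is r = √DE.
- CBT vs TAU: true SE = √(DE/132 + 1/51), so r = √[(DE/132 + 1/51) / (1/132 + 1/51)].
- Type I error of the unadjusted test = 2 × [1 − Φ(1.96/r)].
- Power of a correctly sized test = Φ(δ/true SE − 1.96).

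Worked case, m = 6 and ICC 0.05: DE = 1.25. For CBT vs SH, r = 1.118 and the type I error is 8.0%. For CBT vs TAU, r = √(0.02908/0.02718) = 1.034 and the type I error is 5.8%.

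| m | ICC | DE | CBT vs SH: type I | CBT vs SH: power | CBT vs TAU: type I | CBT vs TAU: power |
|---|---|---|---|---|---|---|
| 4 | 0.01 | 1.03 | 5.3% | 89.3% | 5.1% | 95.2% |
| 6 | 0.05 | 1.25 | 8.0% | 82.8% | 5.8% | 94.0% |
| 6 | 0.10 | 1.50 | 11.0% | 75.6% | 6.6% | 92.6% |
| 8 | 0.10 | 1.70 | 13.3% | 70.3% | 7.3% | 91.4% |

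CBT vs TAU moves little because the 51 unclustered TAU patients supply most of the variance: 1/51 = 0.0196 against 1/132 = 0.0076.

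**Step 3: if SH had no clustering.** Then r = √[(DE + 1)/2] for CBT vs SH. At m = 6 and ICC 0.05 the type I error is 6.5% and power 86.5%.

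**Step 4: credit for the baseline score.** The t-test takes no credit for it, but the planned model includes it. Assume a baseline correlation of 0.5, so that residual variance falls by the factor 1 − 0.5² = 0.75, and take the ICC as that of the adjusted score.

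- DE 1.25: 0.75 × 1.25 = 0.9375; power = Φ(0.4/√(2 × 0.9375/132) − 1.96) = 92%.
- DE 1.50: 0.75 × 1.50 = 1.125; power 87%.

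The correlation that just cancels the loss is √(1 − 1/DE): 0.45 and 0.58 respectively. This scales the naive and the true SE alike, so r and the type I error do not change.

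**The case against.** The case for leaving the plan alone has several parts.

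- **The ICC is unknown and may be small.** This stands. At ICC 0.01 with groups of 4, the CBT vs SH test runs at 5.3%, which is negligible. The size of the problem can only be given as a range.
- **The primary hypothesis is hardly touched.** This stands. CBT vs TAU is named as the primary hypothesis, and its error rate stays between 5.1% and 7.3%. The larger figures belong to CBT vs SH, which is tested only if the first test succeeds.
- **Power need not fall.** This stands in part. Step 4 shows that baseline adjustment can offset the loss, so a reader should not infer that power must end below 90%. It does nothing for the error rate.
- **Centre may be added to the model.** This does not help. It is optional, and a centre term does not identify therapy groups.
- **A full analysis plan may specify a mixed model.** It may, but the article states both the model and the sample-size method, and the point concerns those statements.

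Two stronger readings are tempting but unsupported. One is that both arms meet in groups of 4 to 8: that size is given for CBT only. The other is that patients keep the same group and the same leader through the whole 12 weeks and the following 12 months: the article gives the session frequency but does not say that groups or leaders stay fixed.

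**Conclusion.** The point holds in a limited form. Two of the three arms are treated in groups, while the stated regression and the sample size assume independent patients. With any positive therapy-group ICC the two-sided 5% level is not held.

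The effect is potentially material for CBT vs SH, with a type I error of 5.3% to 13.3%, and small to modest for CBT vs TAU, at 5.1% to 7.3%. Before any credit for baseline, power is 89% to 70% for CBT vs SH and 95% to 91% for CBT vs TAU. These ranges rest on an assumed ICC of 0.01 to 0.10, SD 1, SH groups of the same size as CBT groups, and a normal approximation. They do not show that the primary comparison is invalid or that the trial is too small.

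**What to change.** Use the therapy-group identifier in the primary analysis. Replace the ordinary regression by a partially nested mixed model:

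- arm and baseline MCS z-score as fixed effects;
- a random therapy-group intercept in CBT and SH only, with TAU patients unclustered;
- small-sample degrees of freedom, because the groups are few (132/6 = 22 per clustered arm at m = 6).

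State the SH group size, and restate power for both hypotheses over a stated ICC range, saying whether credit is taken for the baseline score. Fix the model before the one-year outcomes are analysed.

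The cost is somewhat wider intervals and a less favourable power statement. Neither treatment nor recruitment changes, and no extra patients are needed to hold the 5% level. Holding 90% power for CBT vs SH on the unadjusted t-test basis would be a separate decision: it would take 132 × DE patients per arm, for example 132 × 1.25 = 165 at m = 6 and ICC 0.05. If the ICC proves close to zero, little is lost.

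### With arms of 132, 132 and 51, the gatekeeping CBT vs TAU test is sensitive to unequal spread between arms; a robust standard error would remove this at almost no cost

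*Protocol article*

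**What the plan says.** The Protocol article, under Analysis of outcome variables, names the confirmatory model for the one-year SF-36 mental component z-score: "We plan to employ a linear regression model of z-transformed SF-36 score on type of intervention and baseline score". Further covariates are optional. CBT vs TAU is ranked first and CBT vs SH second, and "the second hypothesis will be tested at a two-sided 5% level only if the first test is significant at a two-sided 5% level".

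Under Sample size calculation the arms are "132 in CBT, 132 in SH, and 51 in TAU". The effects are set out as follows: "we assume differences of δ = 0.6 between CBT and TAU and of δ = 0.4 between CBT and SH". The calculation is for a two-sided t-test at 0.05, and no SD is given for any arm.

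Under Trial interventions, CBT is a manualised group programme. Of TAU the article says that "any treatment option may be chosen, since care as usual for sub-threshold depression is currently not formalised".

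The article does not say how standard errors will be estimated.

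**The concern.** Ordinary linear regression estimates one residual variance from all patients. Here 264 of the 315 (84%) are in CBT or SH. The precision of CBT vs TAU is limited mainly by the 51 TAU patients, so the variance that matters most for that contrast is taken largely from other arms. If TAU is more variable than CBT and SH, the standard error is too small and the test rejects too often. If TAU is less variable, the test is conservative. The SH spread enters the same pooled estimate, although SH is not part of the contrast.

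CBT vs TAU is the primary hypothesis and opens the way to CBT vs SH. An excess of false positives in the first test would pass straight into the error rate of the hierarchy, and the confidence interval would have the wrong coverage.

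**Working it through.** **Inputs.** From the article: n = 132 (CBT), 132 (SH), 51 (TAU); two-sided α = 0.05; δ = 0.6 and 0.4. Assumed: SD = 1 in CBT and SH, with the TAU SD varied.

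**Reproducing the plan's figures with a common SD of 1.**
- CBT vs SH: n = 2(1.960 + 1.282)²/0.4² = 131.4, so 132 per arm, as stated.
- CBT vs TAU: SE = √(1/132 + 1/51) = √0.02718 = 0.1649. Then 0.6/0.1649 − 1.960 = 1.679, which gives power of 95.3% (95.2% by the exact t), against the stated 95%.

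The plan's numbers thus fit a common SD of 1.

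**Weight against information.** TAU's share of the variance of the contrast is (1/51)/(1/51 + 1/132) = 0.01961/0.02718 = 72%. Its share of the patients behind the pooled variance is 51/315 = 16%.

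**Type I error under unequal spread.**
- Pooled variance: s² = (131·σ²_CBT + 131·σ²_SH + 50·σ²_TAU)/312
- Model SE = √[s²(1/132 + 1/51)]
- True SE = √(σ²_CBT/132 + σ²_TAU/51)
- Error = 2[1 − Φ(1.96 × model SE/true SE)]

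| SD of CBT, SH, TAU | s² | Model SE | True SE | Error |
|---|---|---|---|---|
| 1, 1, 0.8 | 0.942 | 0.1600 | 0.1419 | 2.7% |
| 1, 1, 1 | 1.000 | 0.1649 | 0.1649 | 5.0% |
| 1, 1, 1.04 (variance 1.09) | 1.014 | 0.1661 | 0.1701 | 5.6% |
| 1, 1, 1.2 | 1.071 | 0.1706 | 0.1892 | 7.7% |
| 1, 0.8, 1 | 0.849 | 0.1519 | 0.1649 | 7.1% |
| 1, 1.25, 1 | 1.236 | 0.1833 | 0.1649 | 2.9% |

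Simulating the stated regression with the baseline score (20,000 trials per setting) gave 2.7% at a TAU SD ratio of 0.8, 5.0% at 1 and 8.4% at 1.25, in agreement with the formula. Arms of 106, 106 and 41, as after a 20% loss, give the same rates. With three equal arms of 105, ratios of 0.8 and 1.25 would give only 4.2% and 5.9%, so most of the sensitivity comes from the allocation.

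**How much extra TAU spread does the text support?** Suppose half the TAU patients receive a treatment worth 0.6, the full assumed CBT vs TAU effect. The added variance is 0.5 × 0.5 × 0.6² = 0.09, so the SD is √1.09 = 1.04 and the error is 5.6%. If baseline adjustment removes a quarter of the variance (assumed), the TAU to CBT variance ratio is 0.84/0.75 = 1.12 and the error is about 5.8%. To reach an SD of 1.2, the two halves would have to differ by 2√0.44 = 1.33, more than twice the assumed effect.

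**With the remedy.** HC3 standard errors in the same regression give 4.8%, 4.7%, 5.1%, 5.0% and 4.9% at TAU SD ratios of 0.67, 0.8, 1, 1.25 and 1.5. At δ = 0.6 and equal SDs, simulated power is 95.2% with the pooled variance and 95.0% with arm-specific variances and Satterthwaite degrees of freedom; the gap before rounding is just under 0.3 points.

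**The case against.** The quoted sentence does not commit the trial to a pooled variance. A linear regression with robust standard errors is still a linear regression, and a condensed article may leave the variance estimator to an analysis plan that is not at hand. This stands: nothing in the article is wrong as written, and if the analysis plan already specifies robust or arm-specific variances, the point is closed.

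Nor is unequal spread shown. No arm SD is given, and the plan's own sample sizes imply equal SDs, for which the error is 5.0%. This also stands.

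A reader might infer from the open-ended TAU care that its outcomes must be much more variable and that the primary test really runs at 7% to 9%. The documents do not support that. Treatment mixing of the size the plan assumes gives an SD of about 1.04. Even the direction is open, because varied individual response or shared group effects could widen the CBT spread and make the test conservative.

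What remains is that the article does fix the arm sizes, the model and the gate, and that in its default form this combination depends on an assumption which is cheap to avoid.

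**Conclusion.** This is a low-severity improvement, not an error in the plan. If the regression is run with its usual single residual variance, the level of the CBT vs TAU test depends on equal spread in all three arms, SH included. The departure that the text can plausibly support is about half a percentage point (5.6% against 5.0%), on the assumption that half of TAU receives a treatment worth 0.6 and that the SD is otherwise 1. The values 2.7% and 7.7%, at TAU SD ratios of 0.8 and 1.2, mark an assumed range and are not expected results. No actual inflation is demonstrated.

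**What to change.** Keep the regression, its point estimates, the test order and the sample size. Add one sentence, before outcome data are seen, stating that the tests and 95% confidence intervals for CBT vs TAU and CBT vs SH use HC3 standard errors, or alternatively arm-specific residual variances with Satterthwaite degrees of freedom. Choose one of the two in advance. The cost is about 0.3 points of power for CBT vs TAU if the variances are equal. Neither option deals with correlation within therapy groups, which is a separate question.

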### Trial design

The trial will be conducted as a multicentre, open, observer-blinded, parallel groups (3 groups) randomized controlled trial (RCT). 'Observer-blinded' means that treatment evaluations will be conducted by blinded assessors. Further blinding is not possible, given the comparison of clearly identifiable group interventions with treatment as usual. All eligible type 2 diabetes patients within the age range of 65 to 85 years who give informed consent will be screened at the participating trial sites in the multicentre trial. All patients with minor depression or mild major depression (3 to 6 depression symptoms according to DSM-IV-TR criteria) will be included in the trial, provided that they meet the other inclusion and exclusion criteria. Patients included in the MIND-DIA trial will be randomized to one of the three treatment conditions: CBT, SH or TAU. In all groups patients will receive diabetological treatment as usual by their treating physicians during the trial. After 12 weeks of open-label therapy, both group interventions will be reduced to one session per month in the long-term phase of the trial (12 additional months). At the 12-month follow-up, all groups will be re-examined regarding the primary outcome variable and all secondary variables. A first analysis is planned after the end of the short-term phase of the RCT without the analyses of the parameters for depression and HRQoL. Therefore, this interim analysis will not influence the primary results or the conduct of the trial. For the first funding phase, the duration of the MIND-DIA trial is expected to be approximately 36 months. Recruitment of patients started in May 2009. The trial design is shown in figure 1.

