### Outcome measures

The primary outcome variable is HRQoL as measured by the Short Form-36 [32]: z-values will be obtained by z-transformation of the SF-36 Mental Component Summary score based on means and standard deviations of age- and gender-matched reference groups from the German general population. This transformation will be performed because it is known that in some respects HRQoL decreases differently with age for men and women. Because the level of depressive symptoms is already relatively low in patients with subthreshold depression compared with patients who have major depression (notwithstanding a comparably low HRQoL), the possibility for improvement is reduced ('bottom effect'). Hence, when one assesses the efficacy of an intervention in this specific group, it seems reasonable to analyse, in additional studies, other important variables, e.g. HRQoL, as the primary outcome variable and depressive symptoms as a secondary variable among others. Results of our own research demonstrated that HRQoL is extremely reduced among diabetes patients with depressive symptoms: Differences in SF-36 z-values were -1.4 for the physical and -1.9 for the mental component, a finding that indicates that a bottom effect is not to be expected in HRQoL.

Secondary outcome variables are: HRQoL (physical component as measured by the Physical Component Summary Score), reduction of depressive symptoms (Quick Inventory of Depressive Symptomatology-Clinician Rated, QIDS-C-16 [33]; Hamilton Depression Scale, HAMD [34]), prevention of moderate/severe major depression (Depression module, SCID), improvement of glycaemic control (HbA1_c_), prevention of mortality, and cost-effectiveness. Standardised rater training of evaluators who were blind to treatment conditions was carried out for observer-derived depression assessments (QIDS-C, HAMD, SCID).

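### Carrying the last observation forward counts dropouts as free of moderate/severe major depression, so the reported proportion understates onset and can mislead between arms if loss is unequal

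*Protocol article*

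**What the plan says.** Two places in the protocol article give the missing-data rule. The section Sample size calculation says "The last observation carried forward method (LOCF) will be used for the handling of missing data due to dropouts", for an analysis set that "includes all randomised subjects in the groups to which they were assigned". The section Analysis of outcome variables repeats that "the last observation carried forward method will be used for the handling of missing data". Neither exempts an outcome.

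The sentence after the second statement turns to the secondary outcomes and ends "prophylaxis of moderate/severe major depression, glycaemic control (HbA1c), and mortality) will be analysed primarily in a descriptive manner". Two analyses then bear on onset of moderate/severe major depression:

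- as a binary outcome: "For binary response variables, the numbers and proportion of responders will be presented together with 95% confidence intervals for the proportions", with logistic regression adjusted for baseline values if arms are compared;
- as a time-to-event outcome: "Time to onset of moderate/severe major depression and conversion rates to dementia will be analysed using Kaplan-Maier estimates".

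The Outcome measures section names the instrument: "prevention of moderate/severe major depression (Depression module, SCID". Table 1 schedules that module at baseline, M3 and M15 only. The Trial design section restricts entry to "minor depression or mild major depression (3 to 6 depression symptoms according to DSM-IV-TR criteria", so no patient has the event at baseline.

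Expected loss to follow-up is 20% overall, attributed partly to mortality and not split by arm. Sensitivity analyses with other imputation methods are promised, but the methods are not named.

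**The concern.** For a score such as the SF-36 mental component, the value carried forward may be too high or too low. For the first onset of a condition that nobody has at entry, the error has one direction: it can hide an event but never create one. A patient lost before M3 carries a guaranteed non-event to the end. A patient lost between M3 and M15 carries the M3 status across twelve months without a scheduled SCID. A patient who dies without an observed onset would also be carried as a non-event.

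The reported proportion with onset is then too low in every arm, and more so in an arm that loses more patients. Adjusting for the baseline value of this endpoint changes nothing, because that value is the same for everyone. Prevention of moderate/severe major depression with CBT compared with TAU is one of the stated secondary hypotheses, so readers will look at this figure.

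**Working it through.** **The plan's own figures.** The article gives no expected risk or power for this endpoint. Its sample size for the primary outcome reproduces: a difference of 0.4 (SD 1, two-sided 5%, 90% power) needs 132 per group, and 132 against 51 with a difference of 0.6 has 95.2% power (noncentral t) to 95.3% (normal). Those figures are not in question.

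**Inputs from the article.** Loss of 20% overall; SCID at baseline, M3 and M15; all patients event-free at entry; 132 patients in CBT and 51 in TAU.

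**Assumptions, because the article gives no values.**
- p = true risk of onset by M15, taken as 15%.
- d = proportion lost, by arm.
- s = share of the losses that occur before M3.
- f = share of all events already seen at M3.
- Dropout is independent of outcome.

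**Formula.** Patients with complete follow-up contribute p(1 − d). Those lost before M3 contribute nothing. Those lost after M3 contribute only events seen at M3. So

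risk shown under LOCF = p(1 − d) + d(1 − s)pf.

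Two cases are shown. If all loss is before M3 (s = 1), this is p(1 − d). If all loss is after M3 (s = 0) with f = 0.3, it is p(1 − 0.7d).

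| Loss, arm A / arm B | All before M3 | All after M3, f = 0.3 |
|---|---|---|
| 20% / 20% | 0.15 × 0.80 = 12.0% in both; RR 1.00 | 0.15 × 0.86 = 12.9% in both; RR 1.00 |
| 25% / 15% | 11.25% / 12.75%; RR 0.75/0.85 = 0.88 | 12.4% / 13.4%; RR 0.825/0.895 = 0.92 |
| 30% / 10% | 10.5% / 13.5%; RR 0.70/0.90 = 0.78 | 11.85% / 13.95%; RR 0.79/0.93 = 0.85 |

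The true risk is the same in both arms throughout. The risk p cancels from the ratio, so the ratios do not depend on the 15%. The bias shrinks as more events are seen by M3.

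**Direction.** The bias favours whichever arm loses more. With 10% loss in CBT and 30% in TAU the ratio turns against CBT: 0.90/0.70 = 1.29, or 0.93/0.79 = 1.18.

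**Effect on a nominal test.** In 20,000 simulated trials of 132 against 51 patients with equal true risk, 30% against 10% loss and all loss before M3, a two-sided 5% test rejected in about 11% of trials at a true risk of 20% and about 14% at 30%, almost always favouring the arm with more loss. With 20% loss in both arms and a risk of 20%, it rejected in 4.6%.

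**Censoring instead.** With dropouts censored at their last SCID, the conditional risk is pf up to M3 and p(1 − f)/(1 − pf) from M3 to M15. The cumulative risk is 1 − (1 − pf) × [1 − p(1 − f)/(1 − pf)] = p. With p = 0.15 and f = 0.3: 1 − 0.955 × (1 − 0.105/0.955) = 1 − 0.85 = 0.15. Under independent dropout the true risk is recovered whatever d is.

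**The case against.** The strongest reply is that the plan already contains the remedy. The Kaplan-Meier analysis of time to onset would normally censor dropouts and so give the right risk when dropout is non-informative. This largely stands, and nobody should read the protocol as having only an LOCF analysis of this endpoint. But the proportion and any logistic model remain alongside it, the text does not say which leads, and the two could disagree on the same endpoint.

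A second reply is that LOCF was meant only for the primary outcome: its sentence follows the two ordered hypotheses, and its other mention is under the sample size. The reach is indeed read from unrestricted wording, and no sentence applies LOCF to the SCID by name. Still, the rule is stated for the analyses generally, and the secondary outcomes follow directly with no exemption. This is a rule stated too broadly rather than a detail left to the analysis plan.

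Third, the outcome is descriptive, its p-values are expressly non-confirmatory, and sensitivity analyses are promised. All true, and this limits the weight of the point. LOCF nevertheless remains the main rule.

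Several stronger readings are tempting but unsupported:
- **That the trial will show false protection.** This needs loss that differs by arm. Attending weekly sessions in one arm and not in another makes that plausible, but the article gives only 20% overall, and equal loss leaves the ratio at 1.0.
- **That incidence is always multiplied by one minus the dropout rate.** That is the extreme case, with all loss before M3 or no events seen by then.
- **That mortality is distorted in the same way.** Nothing shows that vital status would be carried forward.
- **That the primary result is affected.** It is not.

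**Conclusion.** The point holds in limited form. Followed as written, the LOCF rule makes the proportion with onset of moderate/severe major depression too low. At the stated 20% loss, an assumed 15% is shown as 12% to 12.9%, without a spurious difference between arms. A false risk ratio of 0.78 to 0.85 (30% against 10% loss) or 0.88 to 0.92 (25% against 15%) arises only if loss differs by arm, and those splits are assumptions. So are the 15% risk, the timing of loss and the 30% of events seen by M3.

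The calculations take dropout as unrelated to outcome. With loss before M3, the part missed is the proportion lost times the risk among those lost, so the understatement grows if patients who are worsening tend to leave. In that case simple censoring would not be fully unbiased either, which is why the fix includes a sensitivity analysis. The consequence is confined to a secondary, descriptive outcome.

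**What to change.** Amend the analysis wording as follows:

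1. State that LOCF does not apply to onset of moderate/severe major depression.
2. Make the already planned time-to-onset analysis the main one for this endpoint. Censor dropouts at their last SCID, allow for onset being known only to lie before M3 or between M3 and M15, and treat death as a competing event. Multiple imputation by arm, using QIDS/HAMD and SF-36 as predictors, is an acceptable alternative.
3. Derive the reported proportions and their confidence intervals from the same approach, so that the endpoint has one consistent estimate.
4. Name one sensitivity analysis that counts dropouts as events, so that readers can see how far the conclusion depends on those lost.

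No new data or visits are needed. The cost is the wording and slightly wider intervals, because dropouts no longer count as fully observed.
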